### ICD-10 classification of depression

These criteria are to be used in interviews with GPs to identify eligible patients and to grade the severity of depression.

The severity of a depressive episode is:

• mild (F32.0): at least two typical symptoms, plus at least two other common symptoms; none of the symptoms intense

• moderate (F32.1): at least two typical symptoms, plus at least three other common symptoms; some symptoms marked

• severe (F32.2): all three typical symptoms, plus at least four other common symptoms; some symptoms severe with intensity

• severe with psychotic symptoms (F32.3); as described in F32.2 but with delusions, psychomotor retardation or stupor so severe that ordinary social activities are impossible

A recurrent depressive disorder (F33) is where there are recurrent depressive episodes. Persistent mood disorders (F34.1) are known as dysthymia. An abridged depressive episode has a minimum duration of episode of about two weeks.

Typical symptoms (the core symptoms) are: depressed mood, loss of interest and enjoyment, reduced energy and increased fatigability.

Other common symptoms are: reduced concentration and attention, reduced self-esteem and self-confidence, ideas of guilt and unworthiness, agitation or retardation, ideas or acts of self-harm or suicide, disturbed sleep and diminished appetite.

### Implementation program

#### Development of the implementation program

In previous phases of the TICD project, we identified determinants for the implementation of the recommendations as well as strategies to address those determinants. This process is reported in detail elsewhere [25]. After prioritisation of the six recommendations, we discussed these in focus groups with health-care professionals, individual interviews with health-care professionals and patients, and we sent a survey to health-care professionals across the country. Numerous determinants of practice were identified. Using a standardised prioritisation method, which was also used by the other participating research groups in the TICD project, we prioritised 23 determinants. These determinants were discussed with implementation scientists, quality improvement professionals, stakeholder groups, general practitioners, nurses in primary care and relatives of elderly patients with depression, to suggest interventions that addressed the identified determinants. After prioritising and grouping the interventions that were suggested, we developed a comprehensive package of tailored interventions (the TICD package), in which each strategy addresses one or more specific determinants.

#### The logic model

The tailored interventions will consist of a package of strategies selected to address key determinants that we identified, which we assume affect the potential to improve the care of elderly patients with depression in primary care. A total of 52 strategies, addressing one or several determinants will be implemented. This package of strategies includes the following components:

1. Support for the development of a collaborative care plan by the municipality, including the management of elderly patients with moderate to severe depression.

a. Development of the plan: We will develop strategies that provide municipalities with tools and checklists for developing a collaborative care plan, including a list of the types of key personnel who should participate and in which form the recommendations should be presented to professionals in the municipality.

b. Content of the plan: We will provide a checklist of the content, including advice on the responsibility of health-care professionals, information on the availability of psychotherapy for moderately or severely depressed elderly patients, information about establishing services regarding depression care managers in the community, how to access voluntary services and a plan for dissemination and implementation of the plan. Resources for general practitioners and other health-care professionals. We will provide information on alternatives to antidepressants for mild depression, tools for counselling, tools for referral to depression care managers and psychotherapists and other tools and information that may help health-care professionals adhere to the recommendations.

2. Resources for patients and their relatives. We will provide information on alternatives to antidepressants for mild depression and evidence for counselling in depression and the combination of antidepressants and psychotherapy for severe depression, recurrent depression, chronic depression and dysthymia. Outreach visits to GP practices or GPs’ educational groups. We will discuss the recommendations with GPs, and adapt the content of the visits according to the needs of each practice. We will discuss how GPs prescribe antidepressants for mild depression and their feeling of having limited time. We will discuss the possibility for extended consultations and relevant fees for assessing the severity of depression and any other factors relevant for adherence to the recommendations.

3. Educational resources. We will provide information on training in cognitive behavioural therapy and counselling, and we will develop e-learning courses. We will provide resources for volunteers who need to improve their communication with depressed patients.

4. Data systems. We will develop a comprehensive website, with educational resources and tools for health-care professionals, patients and relatives.

Figure 2 illustrates how the various components in the package target various levels of the health-care system.

**Figure 2 F2:**
[figure not shown]
**How the interventions target various levels of the health-care system.** GP, general practitioner; HCP, health-care professional.

For a detailed description of the strategies, and their relation to the determinants of practice and recommendation, see Additional file 1: Appendix B.

We have not addressed determinants and interventions that we considered unrealistic within this study. An example is the determinant ‘lack of health-care professionals to provide psychotherapy’ and the suggested intervention ‘employ more professionals who can provide psychotherapy’. Additionally, we omitted all suggested interventions that could compromise the randomised design of the trial, such as using the media (radio, newspapers and so on) and electronic resources available to all health-care professionals, such as the Norwegian Electronic Medical Handbook and the Norwegian Electronic Health Library.

### Outcome/measures

#### Primary outcome

The primary outcome is the proportion of recommendations that are implemented by the general practitioners. We will interview GPs to obtain this information for up to six included patients. The proportion of the prioritised recommendations adhered to for each patient will be measured. The questions for the GP will depend on the severity of the patient’s depression.

Mild depression (seven questions)

1. Did the GP offer the patient a self-help programme (web-based, book or course)?

2. Was the patient offered antidepressants? If yes, has the patient previously responded to antidepressants when moderately or severely depressed?

For questions 3 to 7, the GP will be asked if they discussed each of the following topics with the patient, and if the patient experienced the problem, were they offered advice about how to address the problem.^a^

3. Lack of social contact

4. Sleep problems

5. Lack of physical exercise

6. Anxiety

7. Difficulties problem-solving

Moderate depression (seven questions)

1. Did the GP offer the patient a self-help programme (web-based, book or course)?

2. Was the patient referred to a case manager?

For questions 3 to 7, the GPs will be asked if they discussed each of the following topics with the patient, and if the patient experienced the problem, were they offered advice about how to address the problem.^a^

3. Lack of social contact

4. Sleep problems

5. Lack of physical exercise

6. Anxiety

7. Difficulties problem-solving

Severe depression (two questions)

1. Was the patient referred to a case manager?

2. Were antidepressants prescribed and was the patient offered psychotherapy?

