#### Severe depression, recurrent depression, chronic depression and dysthymia

Primary-care physicians should offer these patients a combination of antidepressant medication and psychotherapy. If the physician is not trained to provide the patient with psychotherapy, patients should be referred to trained health-care professionals.

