### Eligibility criteria

All practising GPs in the included municipalities are eligible. Eligible patients will be identified by extracting information from GPs’ electronic medical records, using an algorithm based on the diagnostic codes in the International Classification of Primary Care, 2nd edition (ICPC-2). It is mandatory for Norwegian GPs to use this classification system in their contact with patients. Furthermore, the algorithm will contain ICPC2 diagnostic text, free text, prescription of antidepressants and billing codes. We will use several criteria to identify depressed elderly patients, even if they do not have a recorded diagnosis of depression, because many practitioners will use other diagnostic codes. The algorithm will give a score from one to six, the lower score indicating a lower probability that the patient is suffering from depression. A definite diagnosis and assessment of the severity of a patient’s depression will be based on the International Statistical Classification of Disease and Related Health Problems (ICD-10) [30] (in order to distinguish each case with regard to depression severity (mild, moderate or severe) and whether the patient suffers from recurrent or chronic depression or dysthymia. Patients will be excluded if they have a diagnosis of dementia, bipolar disorder or reside in nursing homes or are assessed by their practitioner to have low life expectancy.

From each GPs’ list we will choose a total of six patients with depression. Each list will be sorted using the score from the algorithm. We will choose patients from the top of the list. If a list contains more than six patients with a score of six, we will select from those patients randomly. If any of the first six patients identified do not suffer from depression according to the ICD-10 criteria, we will chose more patients from the list, until we have identified six patients with depression according to the ICD-10 criteria.

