### Statistical methods

The primary outcome of interest for our analysis is the mean adherence rate per GP (based on six patients). We will assess the number of recommendations that were followed with regard to the severity of depression, and we will calculate an overall mean for adherence across disease severity for each GP. For mild and moderate depression there are seven recommendations and for severe depression there are two recommendations; these will be assessed by interviewing the GP, who will have access to patients’ medical records during the interview. The analysis will be performed as an intention-to-treat analysis; we count all GPs in the group to which they were assigned, regardless of whether they received the intervention or not.

All analyses will be performed in SAS version 9.2 (SAS Institute Inc.) using PROC GLIMMIX with random effects for municipality and practice to account for the clustered nature of the data. Continuous data will be analysed assuming that the data follows a normal distribution (linear regression) and dichotomous data will analysed using the binomial distribution (logistic regression). In the initial analyses only the allocation to intervention or control will be included as an independent variable in the analysis (Intervention = YES/NO).

The following factors and variables are assumed to be effect modifiers: whether the municipality already has a collaborative plan (may improve adherence), whether access to cognitive behavioural therapy is poor (may reduce adherence), whether municipalities belong to the ‘Centre for Development of Institutional and Home Care Services’ network (may improve adherence) and whether GP has many elderly patients on the list (may improve adherence).

Each of the pre-specified effect modifiers will be separately included as independent variables (alongside allocation to intervention or control) in the model. All the effect modifiers with *P* < 0.3 in the previous step will be included as independent variables in a final multivariate model.

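### The primary score asks about combined treatment only in the severe set, so non-severe recurrent or chronic patients are never scored on the sixth recommendation and dysthymia has no item set

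*Protocol article*

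**What the plan says.** The last of the six recommendations in the Protocol article's Background names severe, recurrent and chronic depression and dysthymia, and says: "Primary-care physicians should offer these patients a combination of antidepressant medication and psychotherapy".

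Eligibility criteria says that the ICD-10 assessment will establish each patient's severity grade and also "whether the patient suffers from recurrent or chronic depression or dysthymia". The section ICD-10 classification of depression grades episodes by symptom counts and intensity. It then lists recurrent disorder and dysthymia under separate codes: "Persistent mood disorders (F34.1) are known as dysthymia". Participants and settings includes recurrent depression among the inclusion diagnoses but mentions neither chronic depression nor dysthymia.

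Primary outcome fixes the score: "The questions for the GP will depend on the severity of the patient’s depression". It gives a mild, a moderate and a severe set. The only question on combined treatment is the second item of the severe set: "Were antidepressants prescribed and was the patient offered psychotherapy". Statistical methods repeats the structure: "For mild and moderate depression there are seven recommendations and for severe depression there are two recommendations". Sample size, however, speaks of seven or eight recommendations per patient.

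**The concern.** The outcome is meant to measure how far GPs follow the six recommendations. The sixth is defined partly by course of illness (recurrent, chronic, dysthymia), whereas the score is organised by severity only. A patient can belong to the sixth recommendation's target population and never be asked about it.

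The trial intervenes on this very point. The logic model promises patients and relatives material on combined treatment for all four groups, and the Usual care section says that most of these patients get drug treatment without adequate psychotherapy. If the intervention improved that care outside severe episodes, the primary outcome would not register it. For some currently mild patients the score could even fall. Outcome data come from GP interviews that begin three months after the intervention, so a question not asked then may not be recoverable.

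**Working it through.** **Item counts.** Counting the questions under Primary outcome:
- mild: self-help 1 + antidepressant 1 + topics 5 = 7
- moderate: self-help 1 + case manager 1 + topics 5 = 7
- severe: case manager 1 + combination 1 = 2

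This reproduces the 7/7/2 in Statistical methods. No set has eight items, so the seven or eight in Sample size does not match.

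**Target groups against item sets, applying the stated rule literally.**

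| Patient | In the sixth recommendation? | Item set | Combination item asked? |
|---|---|---|---|
| Severe episode | yes | severe (2) | yes |
| Recurrent or chronic, graded moderate | yes | moderate (7) | no |
| Recurrent or chronic, graded mild | yes | mild (7) | no |
| Dysthymia | yes | none stated | undefined |

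**The mild antidepressant item.** Its scoring direction is taken from the mild-depression recommendation, which advises against antidepressants unless the patient responded to them earlier when moderately or severely depressed. Take a recurrent or chronic patient, currently mild, without such a response, who is offered the combination. The combination earns nothing, and the antidepressant item is failed. That item carries 1/7 = 0.143 of the patient's score.

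**Numbers of patients.** The planned totals reproduce: 80 municipalities × 10.93 GPs × 0.5 consenting = 437.2, stated as 437 GPs; 437 × 6 = 2,622 patients at most. The article gives no case mix, so the number affected cannot be derived. Assumed shares of 10% to 50% would be 0.10 × 2,622 = 262 to 0.50 × 2,622 = 1,311 patients.

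**Illustration of size.** Let s be the share of audited patients who are non-severe and recurrent, chronic or dysthymic (assumed 0.10 to 0.50), r the rise in combination offers among them (assumed 0.20), and k the number of items if the combination is added to a seven-item set (8). The item's contribution to the mean score is s × r / k:
- s = 0.10: 0.10 × 0.20 / 8 = 0.0025
- s = 0.30: 0.30 × 0.20 / 8 = 0.0075
- s = 0.50: 0.50 × 0.20 / 8 = 0.0125

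For patients who have a defined set, the score as written registers 0 whatever s and r are. Where dysthymia would count is not defined.

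**The case against.** **The score may be a deliberate composite.** It already tailors items by severity. The severe set also leaves out social contact and counselling, although those recommendations carry no severity limit. That is fair, and this point does not ask for every recommendation to be scored in every patient. But the sixth recommendation defines its own target groups, and the patient assessment records them. No reason is given for scoring only one of the four.

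**The severe set may have been meant for all four groups, or the interview form may route them.** The article condenses a fuller document and its appendices are not shown. Even so, it fixes the sets and denominators in two places and labels the two-item set severe in both. If a wider use is meant, the text has to say so.

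**Dysthymia and chronic depression are not among the listed inclusion diagnoses.** True, but they are classified when eligible patients are identified, so the sections need reconciling. Recurrent depression is listed, so that gap stands regardless.

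**The gain from the added item may be small.** The plan deliberately did not address the shortage of professionals who provide psychotherapy, so this item may respond less than the others. An eighth item also reduces the weight of the other seven. If those improve by d on average, the net change is s × (r − d) / 8. With d = 0.05, the plan's target difference, this is 0.10 × 0.15 / 8 = 0.0019 to 0.50 × 0.15 / 8 = 0.0094. It is negative if r is below d. This stands: the case for the change is that the score should measure what it claims to, and no gain in power is claimed.

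**Conclusion.** The mismatch is real and lies in the text itself. Followed exactly, the scoring rule gives no credit for the sixth recommendation in non-severe recurrent or chronic patients, can count against care given under it in some who are currently mild, and leaves dysthymia without a set. The consequence is a narrower primary outcome. Its size is unknown; 0.0025 to 0.0125 is an illustration that rests on assumed shares and an assumed 20-point rise. No new sample size follows.

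Three stronger readings are tempting but not supported:
- *The comparison is biased.* The same sets apply in both arms, so the omission alone favours neither.
- *Unblinded interviewers can choose the set.* For recurrent and chronic episodes the severity grade decides. Only dysthymia leaves a choice open, and nothing shows that it would be made differently by arm.
- *One patient's set can outweigh the target effect.* A patient given the combination and nothing else scores 0/7 on the moderate set and 1/2 on the severe set, which moves a six-patient GP mean by 0.5/6 = 0.083. That is one GP under an extreme care profile, whereas 0.05 is a difference between arms. At 4/7 against 1/2 the move is 0.071/6 = 0.012.

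Nor does the roughly 30% risk of a chronic episode quoted in the Background give the share of audited patients affected. It is a prognosis and says nothing about the case mix.

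**What to change.** Before outcome interviews start:

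1. State in Primary outcome which item set each recurrent, chronic or dysthymia patient receives, using the classification already described in Eligibility criteria.
2. Add the combination item for non-severe patients to whom the sixth recommendation applies.
3. Define an item set for dysthymia, or state that these patients are not included, and reconcile Participants and settings, Eligibility criteria and ICD-10 classification of depression accordingly.
4. For recurrent or chronic patients who are currently mild, reconcile the mild-depression recommendation, the sixth recommendation and the mild antidepressant item before that item is scored. Which clinical rule applies is for the investigators to settle.
5. Restate the denominators in Statistical methods and the seven or eight recommendations in Sample size so that they agree with the final sets.

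The cost is one added interview question, a mapping rule and corrected denominators. No patients or visits are added. The question has to be on the form when the interviews begin.

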#### Secondary outcomes

We will measure the following patient outcomes for up to six patients for each GP. Most of these outcomes will be assessed by the patients themselves.

1. Global improvement in depression as assessed by the GP using the Clinical Global Impression Scale – Improvement (CGI-I) [31].

2. Improvement in depression as assessed by the patient or a family member:

• Patient Global Impression – Improvement (PGI) [32,33]. CGI-I and PGI are identical measures, using a 7-point Likert scale, where 1 means very much improved, and 7 is very much deteriorated.

• The presence of symptoms of depression and/or anxiety using the Hospital Anxiety and Depression Scale (HADS) [34]. HADS is a 14-item questionnaire, of which seven items measure depressive symptoms and seven items measure anxiety.

3. Loneliness [35,36]

• Do you sometimes experience loneliness? (0 = often, 1 = sometimes, 2 = seldom 3 = never)

4. Social contact

• Did you lack social contact when you first discussed being depressed with your GP? (yes/no)

• If yes, did you subsequently establish social contact with the help of a voluntary organisation or by other means? (0 = no, 1 = once only, 2 = more than once)

5. Physical activity

• Were you physically inactive when you first discussed being depressed with your GP? (yes/no)

• If yes, have you subsequently become more physically active? (yes/no)

6. Sleep problems

• Did you have a problem sleeping when you first discussed being depressed with your GP? (yes/no)

• If yes, has the sleeping problem improved?^b^

7. Anxiety

• Did you have a problem with anxiety when you first discussed being depressed with your GP? (yes/no)

• If yes, has your ability to cope with your anxiety improved?^b^

8. Problem-solving

• Did you have difficulties with problem-solving when you first discussed being depressed with your GP?

• If yes, has your ability to solve problems improved?^b^

9. Use of a self-help programme or reading self-help literature

• Have you used a self-help programme or read self-help literature? (yes/no)

10. Adherence with antidepressants

• Self-reported measure of medication adherence [37,38]

1. Do you ever forget to take your medication?

2. Are you careless at times about taking your medicine?

3. When you feel better, do you sometimes stop taking your medicine?

4. Sometimes when you feel worse, do you stop taking your medicine?

Each ‘yes’ scores 1, a score of 0 suggests no problem with medicine-taking and hence good compliance. The maximum of 4 for the four questions indicates major difficulties and suggests poor compliance.

We will assess whether the following items are present at the municipal level:

1. A collaborative care plan including a plan for elderly patients with depression (document)

2. An identifiable case manager

3. Agreed referral processes

4. Agreed communication processes within primary health-care services

5. Agreed communication processes between primary health-care and specialist health-care services

6. A list of voluntary organisations

7. Awareness of the collaborative care plan (proportion of GPs who are aware of the plan)

8. Knowledge of the collaborative care plan (proportion of GPs who can answer a factual question about the content of the plan)

We will collect data for the first six items above by questionnaires sent to municipality representatives. We will collect data for the last two items during practice visits at the end of the study.

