### Sample size

We plan to include 80 municipalities. We estimate that there are an average of 3.68 practices per municipality and 2.97 GPs per practice (10.93 GPs per municipality), based on data from Statistics Norway and the Norwegian Medical Association. We conducted power calculations for the primary outcome (adherence to recommendations) assuming an alpha of 0.05 (risk of type I error), the ability to detect a minimum difference of 0.05 between the control group and the intervention group regarding GPs’ adherence to the recommendations (the primary outcome: the proportion of recommendations that are implemented by the general practitioners), a standard deviation of 0.17 and an intra-class correlation coefficient (ICC) of 0.02. We assumed that 40%, 50% or 60% of GPs will consent to data collection in samples with 60, 70 or 80 municipalities, respectively. Based on a previous study in which we randomised municipalities, we estimate that the ICC will be less than 0.03 [39]. Based on the assumption that most GPs currently adhere on average to 4 or less of the 7 or 8 recommendations per patient, and a pilot survey of 11 GPs, we estimate that the standard deviation most likely will be less than 0.2.

Based on these assumptions, our calculations indicate that the power to detect a minimum difference in adherence to the recommendations among GPs of 0.05 (scale 0 to 1) in a sample of 80 municipalities is 0.80 provided the standard deviation is 0.17, the ICC 0.02 and 50% of GPs consent to data collection. With 80 municipalities, 437 GPs should be included in the study and this would provide data for at most 2,622 patients. The detailed results of the power calculations are provided in Additional file 1: Appendix D.

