Based on previous studies [40,41] we anticipate that between 40% and 60% of GPs will consent to data collection. All GPs that consent to participate will be asked to mail a questionnaire to each of the six patients that have been identified. Patients will be asked to complete and return the questionnaire by mail. If a patient consents to participate in the study, but does not wish to complete the questionnaire, we will ask the patient to appoint a family member to answer on their behalf if possible. Alternatively the patient may choose to consent to being contacted and interviewed by telephone.

The following data will be collected from patients:

• The patient’s assessment of improvement for depression, anxiety, sleep problems, physical activity, problem-solving, social contact and loneliness (secondary outcome measures)

• Adherence to medication

Each patient, GP and municipality included in the study will receive a unique study ID, which is available to the research group. A list at each GP practice will couple the patient’s study ID and the patient’s national ID number. We will use the patient ID numbers generated by the GPs’ electronic medical records systems. It will be possible for GPs to identify patients using these numbers, but the investigators will not have access to information identifying the patients, unless they first return a mailed consent form with the questionnaire. All communication (for example, letters) with patients will otherwise be through the patients’ GP.

We will collect the following descriptive data from GPs: age, sex, years of clinical experience as a GP, whether they are a specialist in primary-care medicine, competency in using CBT (collected during the structured interviews) and the number of elderly patients (65+) on the patient list.

A schematic presentation of participant timeline and time schedule for data collection is presented in Additional file 1: Appendix E.

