## Endnotes

^a^For these recommendations, we will consider the recommendation implemented if the GP discussed the problem with the patient and the patient did not have the problem or if the patent had the problem and was offered advice

^b^We will use PGI to assess any improvement in sleep problems, anxiety and problem-solving.

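### Change in physical activity is recorded only as yes/no, while the parallel sleep, anxiety and problem-solving items use the 7-point PGI, so the degree of change is lost for this one secondary outcome

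*Protocol article*

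**What the plan says.** In the Protocol article, Secondary outcomes, item 5 begins with a screening question: "Were you physically inactive when you first discussed being depressed with your GP? (yes/no". Patients who answer yes are then asked: "If yes, have you subsequently become more physically active? (yes/no".

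Items 6 to 8 (sleep, anxiety, problem-solving) follow the same pattern of a screening question and then a change question. Their change questions carry endnote b: "We will use PGI to assess any improvement in sleep problems, anxiety and problem-solving". Item 2 of the same list describes the PGI as "using a 7-point Likert scale, where 1 means very much improved, and 7 is very much deteriorated".

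The Data collection section lists what patients will report: "The patient’s assessment of improvement for depression, anxiety, sleep problems, physical activity, problem-solving, social contact and loneliness (secondary outcome measures".

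Under Statistical methods, yes/no outcomes go to a logistic model ("dichotomous data will analysed using the binomial distribution (logistic regression"), whereas outcomes treated as continuous go to a linear one: "Continuous data will be analysed assuming that the data follows a normal distribution (linear regression". Both use mixed models with random effects for municipality and practice. The Sample size section gives power for the primary outcome only.

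**The concern.** Items 5 to 8 ask the same kind of question: did you have this problem, and if so, has it changed? Change in activity comes in degrees, as change in sleep or anxiety does. The questionnaire already carries a graded answer for three of the four items, and the article gives no reason for treating the fourth differently.

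With a yes/no answer, a patient who is slightly more active counts the same as one who is much more active. Everyone else falls into one group, whether unchanged or less active. The format also commits the item to logistic regression and an odds ratio.

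Physical activity is a named counselling topic in the recommendations and one of the five topics on which GPs are scored for mild and moderate depression. It is therefore worth measuring its patient-side counterpart without avoidable loss. This is fixed when the questionnaire is mailed, so an analysis plan cannot repair it afterwards.

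**Working it through.** **The plan's own figure.** The only stated power is 0.80, for GP adherence (difference 0.05, SD 0.17, ICC 0.02, 437 GPs, 80 municipalities).
- With 5.46 consenting GPs per municipality, the design effect is 1 + (5.46 − 1) × 0.02 = 1.089. The effective number per arm is 218.5 / 1.089 = 200.6. Then z = 0.05 / (0.17 × √(2/200.6)) = 2.95, and power = Φ(2.95 − 1.96) = 0.84.
- With all 10.93 GPs per municipality, the design effect is 1.199 and power is 0.80.

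The stated figure is thus reproduced under the second variant. It says nothing about item 5, for which there is no power, effect size, response rate or share of inactive patients to reproduce.

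**Inputs for an illustration.**
- From the article: at most 2,622 patients, 80 municipalities, alpha 0.05 (taken as two-sided), and the ICC of 0.02 borrowed from the primary outcome.
- Assumed: 50% of patients respond and 50% of those were inactive; 'yes' corresponds to PGI 1 to 3; the PGI is analysed as a mean score; the 7-point version has 80% power. The control answers split 15/35/50 within PGI 1 to 3 and 60/20/13/7 within PGI 4 to 7. The intervention shifts an underlying continuous response.

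**Sample.** 2,622 × 0.5 × 0.5 = 655.5 patients. The design effect is 1 + (655.5/80 − 1) × 0.02 = 1.144. The effective number per arm is 655.5 / 2 / 1.144 = 286.5.

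**Worked case: 40% of controls become more active, normal shift.**
- 7-point score: 80% power needs a shift of 0.2415 latent SD. Mean scores are then 3.742 (control) and 3.410 (intervention), with SD 1.417, a difference of 0.234 SD. Check: 0.234 × √(286.5/2) − 1.96 = 0.84, and Φ(0.84) = 0.80.
- Yes/no: the same shift gives Φ(−0.2533 + 0.2415) = 0.495 in the intervention arm. The difference is 0.0953 and its standard error is √((0.4 × 0.6 + 0.495 × 0.505)/286.5) = 0.0414. Then 0.0953/0.0414 − 1.96 = 0.34, and power = Φ(0.34) = 0.635.

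**All control shares, with the 7-point version held at 80% power.**

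| Controls more active | Yes/no power, normal shift | Yes/no power, logistic shift |
|---|---|---|
| 20% | 0.570 | 0.623 |
| 30% | 0.615 | 0.694 |
| 40% | 0.635 | 0.720 |
| 50% | 0.636 | 0.718 |
| 60% | 0.621 | 0.690 |
| 70% | 0.586 | 0.629 |

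The loss is 16 to 23 points under the normal shift and 8 to 18 under the logistic one.

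**How far this moves under other assumptions.**
- Reference power, at 40% of controls: with 50% power for the 7-point score, yes/no power is 0.36 (normal) or 0.43 (logistic). With 99%, it is 0.94 or 0.97, so the loss shrinks to about 2 to 5 points.
- Extreme splits: for a normal variable cut at share p, relative efficiency is φ(z_p)² / (p(1 − p)) and power is Φ(2.80 × √RE − 1.96). At p = 0.5, RE is 0.637 and power 0.61. At p = 0.2, RE is 0.490 and power 0.50. At p = 0.1, RE is 0.342 and power 0.37, a loss of 43 points.
- Fixed effect of 0.2 SD, 30 to 70% inactive and 40 to 80% responding (315 to 1,468 patients), with relative efficiency 0.95 for the 7-point score and 0.576 to 0.64 for yes/no: 7-point power is 0.39 to 0.90, yes/no power 0.26 to 0.75, and the loss about 11 to 21 points.

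Changing the number of patients while re-solving for 80% power leaves yes/no power at 0.63 to 0.64 (236 to 1,285 patients, 40% of controls). This follows from the set-up and is no test of robustness.

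**The case against.** The formats agree with one another. Endnote b is attached to exactly the three items it names, and item 5 states its own format. Nor does the Data collection list promise a common scale: it also contains social contact (three levels) and loneliness (four levels), and self-help use elsewhere is yes/no. One can read the questionnaire as giving the PGI to symptoms and coping, and simpler answers to behaviours. A short answer also suits a brief mailed questionnaire for elderly patients. All of this stands, and it rules out calling the difference an error. It does not show that yes/no is the better format: self-help use is naturally a yes/no event and social contact counts occasions, whereas item 5 asks about change in a state.

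The power comparison assumes that the PGI items are analysed as scores. The article does not say which model they get. If they were reduced to improved or not, most of the gap would vanish. Equating 'yes' with PGI 1 to 3 is likewise an assumption, since no graded activity score is collected and then cut. These points limit the figures to an illustration.

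A reader might infer that this outcome has less power than the sleep or anxiety outcomes. The documents do not support that. Each item is asked only of patients who had that problem, so numbers and effects differ anyway. The calculation compares two formats in the same patients, not two outcomes.

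A reader might also infer that harm would be hidden. It is true that a 'no' cannot show worsening, but only patients already inactive answer, and they have little room to become less active.

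**Conclusion.** The point holds as a minor weakness in one secondary outcome. The yes/no form of item 5 gives up the degree of change when a graded scale is already in the same questionnaire.

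The illustrative loss is about 8 to 23 percentage points of power. It rests on 80% power for a mean-score analysis of a 7-point item, 'yes' meaning PGI 1 to 3, the assumed spread of answers, and 20 to 70% of controls becoming more active. Outside those conditions it runs from about 2 points to more than 40. It would be tempting to quote the normal-shift range of 16 to 23 points as what this trial loses. The documents do not support that, because they give none of the inputs that determine it. The direction is firmer than the size: yes/no lost power in every scenario examined. The primary outcome and its sample size are untouched.

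**What to change.** In Secondary outcomes, item 5, replace the yes/no answer to the second question with the 7-point PGI response, adjusting the stem so that it asks how activity has changed. Add physical activity to endnote b. Analyse the score with the linear mixed model already described under Statistical methods. The proportion answering PGI 1 to 3 can still be reported as 'more active', so nothing available now is lost.

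The cost is one response format and one addition to an endnote. Outcome data are collected only from three months after delivery of the intervention, so the change can be made before any questionnaire is mailed. The downside is a slightly longer answer for elderly patients, in a format that neighbouring items already use.
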